In daily practice, real-time endoscopic recognition of T1 CRC is challenging. Recent Dutch studies demonstrated that endoscopists recognized only 22–39% of all diagnosed T1 CRC as being cancer before endoscopic resection [28, 29]. As result of suboptimal diagnosis, 41% missed potential endoscopic cure due to the selection of inappropriate endoscopic techniques [15, 30]. Conventional polypectomy techniques like piecemeal or *en bloc* snare coagulation often hamper adequate histological assessment leading to uncertainty about the completeness of excision or the presence of histological risk factors. To achieve definite histopathological confirmation about radicality of the resection, or a second chance for radical resection in case of remaining cancer within the bowel wall, an additional endoscopic *en bloc* resection of the previous resection scar might be an attractive strategy. Until recently, no safe endoscopic *en bloc* re-resection technique was available for the re-resection of scar tissue or non-lifting, incomplete resected lesions. The introduction of endoscopic full-thickness resection (eFTR) has expanded the therapeutic endoscopic armamentarium and several large-scale clinical studies have now established its feasibility and safety for complex colorectal lesions [31–34]. The eFTR-technique allows a transmural local excision of the scar and therefore can potentially serve as a valid option for curative completion treatment following incomplete T1 CRC resection, potentially avoiding unnecessary surgical risks [35–40].

eFTR is currently increasingly used for this indication in daily practice. Our previous multicenter feasibility study showed that eFTR of scars of previous R1/Rx resected T1 CRC was technically feasible in 85% with promising short-term results. [25] However, long-term oncologic safety has not been established. By implementing completion eFTR in a prospective national cohort study followed by protocolized surveillance, we aim to assess its feasibility and long-term oncologic safety after previous incomplete resection of low-risk T1 CRC.

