### Objectives

This project aims to investigate the feasibility and oncological safety of endoscopic full-thickness resection (eFTR) as minimal invasive completion treatment after previous R1/Rx endoscopic resection of low-risk T1 CRC. We hypothesize that completion eFTR is feasible in ≥ 80% of patients with a low risk of luminal cancer recurrence < 2%.

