### Outcomes

The primary outcome is to assess the 2- and 5- year local luminal tumor recurrence rate after scar resection by eFTR following a previous R1/Rx resection of low-risk T1 CRC.

The secondary outcomes are:to assess the feasibility of completion eFTR, defined as a macroscopic complete en bloc scar excision in > 80% of casesto assess the percentage of curative eFTR resections, defined as no residual cancer in the scar or in case any residual cancer a R0 resection for T1 CRC without high-risk features (poor differentiation, lymphovascular invasion and/or high-grade tumor budding (grade 2 or 3)to assess the presence of scar tissue and/or complete scar excision at histopathologyto assess the procedure-related adverse event rate and safety of eFTR compared to oncologic surgery in a historical patient-cohort for T1 CRCto assess the 2- and 5- year locoregional nodal and/or distant tumor recurrence rateto assess the 5-year disease-specific survival rate and overall survival rateto assess the 2- and 5-year luminal, nodal and distant tumor recurrence rate in patients not meeting our inclusion criteria, but who did undergo eFTR completion treatment followed by strict surveillance and are included in our observational arm

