#### Histopathology handling

The resection specimen is stretched and pinned down on paraffin or cork before immersed into formalin. Histopathological analysis is performed by a gastrointestinal pathologist according to daily clinical practice. In case of presence of residual adenocarcinoma, deep and lateral resection margins will be assessed as well as all histological risk features (differentiation grade, depth of invasion, lymphovascular invasion and tumor budding (grade 2 or 3)).

In the eFTR specimen, the pathologist will assess the presence of reactive changes compatible with scar tissue in the specimen. Definite histopathological confirmation of complete scar resection is known to be difficult and might not always be possible. In case the pathologist is not able to histologically confirm complete scar resection, further treatment will be based on the macroscopic completeness of scar excision and patients will be followed according to protocol.

In addition, central review of all resected eFTR specimens will be performed after all patients are included in the study. The central review will be performed by two independent expert gastrointestinal pathologists. In this review, the presence of neoplasia, scar tissue and evaluation of completeness of excision regarding both neoplasia and scar will be evaluated by both expert pathologists. In cases without consensus, meetings will be organized to discuss discrepancies to reach consensus. In case no consensus can be reached, a third expert pathologist will be consulted.

H&E slides of all resected eFTR specimens will be collected from the different laboratories and digitalized at the Amsterdam UMC for review. After digitalizing the slides will return to the laboratories to ensure the completeness of pathology archives and optimal patient care.

In case of unexpected findings, the treating physician will be informed to discuss further treatment options with the patients after colorectal MDT discussion. Outcomes of these cases will be recorded in the study database.

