### Sample size

Up-to-date, literature is scarce with regard to local luminal recurrence rates after endoscopic incomplete resection of T1 CRC (R1/Rx resections) for low-risk T1 CRC. A recent study showed local recurrence rates of 4.5% (4/89) after full-thickness resections of incomplete resected presumed low-risk T1 CRC. However, in this study histologic reassessment was not performed before resection and retrospective histologic revision showed high-risk factors for LNM in 3 out of 4 local recurrences [41].

Another study observed a local recurrence rate of 1% (1/102) during almost four years of follow-up after minimally invasive transanal surgery [42]. Considering that literature is limited, the upper limit of its 95% one-sided confidence limit may extend to 4.6%. With already being frequently used in daily practice and considering that the follow-up duration in the current study will by five years (instead of four), we opt to qualify eFTR as unsafe if the upper 95% one-sided confidence limit of its related local recurrence rate after five years extends beyond 6.6%.

A single sample size of 137 patients will have at least 86% power to detect this non-inferiority limit of 6.6% using a one-sided exact test with a significance level of 0.05 for maximum actually observed local recurrence rates of 2% over five years (twice the possibly underestimated local recurrence rate over four years of 1% for minimally invasive surgical treatment). To correct for potential drop-out patients in whom the primary outcome cannot be assessed the sample size will be adjusted to 153 (potential drop-out rate of 10%). These drop-out cases are patients with indication for additional surgery when histopathology review reveals high-risk features (i.e. poor differentiation grade, lymphovascular invasion and/or high-grade tumor budding) for LNM or eFTR is technically impossible. If during 5 years of follow up, more than 5 local luminal recurrences are observed -which implies that the upper limit of the confidence interval will exceed the non-inferiority limit- our study fails to establish oncological safety for completion endoscopic full-thickness resection after previous incomplete resection of low-risk T1 CRC.

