### Statistical methods for primary and secondary outcomes

For our primary analysis all performed eFTR procedures in patients in whom the primary outcome (luminal local tumor recurrence rate after scar resection) can be assessed will be included. Thus patients in whom the procedure could not be performed for technical reasons or needing additional surgery due to the presence of high-risk features following completion eFTR will not be included for primary analysis.

For secondary analysis regarding feasibility of completion eFTR all included eligible patients will be analysed irrespective of the received completion eFTR or performed additional surgery.

Descriptive statistics will be used to describe patient, colonoscopy and eFTR characteristics for primary and secondary outcomes. Variables will be reported as mean with standard deviation in case of continuous and normally distributed variables, as median with an interquartile range (IQR) in case of non-normally distributed continuous variables, and as percentages in case of count or categorical variables. will use logistic regression with baseline variables to identify predictors for a successful completion eFTR.

The confidence interval of the 5 year disease-specific survival rate and overall survival rate will be calculated. Kaplan–Meier analysis will be used to estimate survival over time.

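### The 10% loss allowance sits uneasily with the 85% feasibility the article reports, and the stated 86% power is a local peak that 153 enrolled patients do not secure

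*Protocol article*

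**What the plan says.** The Sample size section asks for 137 assessable patients. It claims power of at least 86% from a one-sided exact test at level 0.05, for a true five-year recurrence rate of 2% against a limit of 6.6%. The decision rule is to "qualify eFTR as unsafe if the upper 95% one-sided confidence limit of its related local recurrence rate after five years extends beyond 6.6" per cent.

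For patients in whom "the primary outcome cannot be assessed the sample size will be adjusted to 153 (potential drop-out rate of 10" per cent), the section then defines who is lost: "These drop-out cases are patients with indication for additional surgery when histopathology review reveals high-risk features", or those in whom eFTR is technically impossible. The Statistical methods section removes the same two groups from the primary analysis, including "patients in whom the procedure could not be performed for technical reasons".

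Two feasibility figures appear elsewhere. The Background says of the team's previous multicentre study that "eFTR of scars of previous R1/Rx resected T1 CRC was technically feasible in 85% with promising short-term results". The Objectives hypothesise feasibility in at least "80% of patients with a low risk of luminal cancer recurrence". The Outcomes section gives feasibility its meaning for this study: "defined as a macroscopic complete en bloc scar excision", in more than 80% of cases.

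**The concern.** One allowance of 10% has to absorb two kinds of loss. The only empirical figure in the article that bears on the first kind, technical failure, leaves 15% not feasible in the same indication. If most of those patients drop out of the primary analysis, the allowance is spent before anyone is lost to surgery for high-risk features.

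The design has little tolerance for this. The exact test moves in whole recurrences, and 137 sits on the edge where the permitted number changes. Falling just below it costs one permitted recurrence and a large step in power. At stake is the chance that a procedure with a true 2% recurrence rate is shown to meet the limit after five years of follow-up.

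**Working it through.** **Inputs.** From the Sample size section: limit 6.6%, one-sided level 0.05, exact test, true rate 2%, 137 assessable, 153 enrolled, 10% loss. From the Background: 85% technically feasible, so 100% − 85% = 15% not feasible.

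**Reproducing the plan's figures.** For x recurrences among n patients, the exact one-sided 95% upper limit is the 0.95 quantile of Beta(x + 1, n − x). The cut-off c is the largest x whose limit does not exceed 6.6%. Power is P(X ≤ c) for X ~ Binomial(n, 0.02).

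- n = 137, x = 4: limit 6.557%, which passes. Attained level P(X ≤ 4 | 6.6%) = 0.048. Power = 0.859, the stated 86% after rounding.
- Inflation: 137 / 0.90 = 152.2, rounded up to 153.

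Both figures reproduce, so the arithmetic is sound. The question is the 10% that goes into it.

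**The budget.** 153 − 137 = 16 patients. The seventeenth loss breaks it: 17 / 153 = 11.1%. Technical failure alone does this if 11.1 / 15 = 74% or more of the earlier study's non-feasible share cannot be assessed. If only half of the 15% is lost (7.5% of 153, about 11 patients), about 5 places remain for surgery after high-risk histology.

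**The edge at 137.** At n = 136, 4 recurrences give an upper limit of 6.604%, which fails. The cut-off is therefore 3 for n = 116 to 136 and 4 for n = 137 to 153.

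| Assessable n | Cut-off | Power at true 2% |
|---|---|---|
| 153 (no loss) | 4 | 80.7% |
| 138 | 4 | 85.6% |
| 137 | 4 | 85.9% |
| 136 | 3 | 71.0% |
| 130 (15% loss) | 3 | 73.7% |
| 122 (20% loss) | 3 | 77.2% |
| 116 | 3 | 79.7% |

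Within each band power falls as n rises, because the permitted count stays fixed. Across n = 116 to 153, only 137 and 138 round to 86%.

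**Expected power at 153 enrolled.** The number lost will vary, so take losses as Binomial(153, d) and average the power over the resulting n:

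| Loss rate d | Expected assessable | Chance of fewer than 137 | Average power |
|---|---|---|---|
| 7.5% | 141.5 | 7% | 83.5% |
| 10% | 137.7 | 36% | 80.3% |
| 15% | 130.1 | 93% | 74.7% |
| 20% | 122.4 | 99.9% | 75.3% |

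The 20% row only shows the range; the article does not predict that loss.

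**The case against.** The strongest objection is that feasibility and assessability differ. In this study, feasibility means a complete en bloc excision of the scar on macroscopic view. An eFTR that was performed but left scar behind is not feasible in that sense, yet it is not among the listed losses. The earlier study's definition is not given in the article. The criteria here (scar or residual lesion of at most 15 mm, excluded sites, at least 10 personal eFTR procedures per endoscopist) may also improve on 85%. All of this stands. It is why the point is conditional on how much of the 15% stays assessable. It does not settle the matter, because the article gives no split that would bring 15% down to 10% or below with room for high-risk surgery.

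A reader might go further and infer from the Objectives that the team accepts a 20% loss while budgeting for 10%. The article does not support that. The 80% is a threshold for success on the feasibility outcome, not an expected rate of loss from the primary analysis. Nor is the missing rationale for 10% a fault in itself, since a condensed article commonly leaves that to the full protocol.

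A second objection is that much of the drop from 86% comes from the stepwise exact test rather than from extra losses. This also stands. With no loss at all, power is 80.7%. Moving from 10% to 15% loss lowers average power by 80.3 − 74.7 = 5.6 percentage points, not by the whole gap to 86%. But the article offers 86% as a minimum, and 153 enrolled does not secure it even when 10% is exactly right.

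A third objection is that the printed failure rule of more than 5 recurrences would give 94.2% power at n = 137 and 95.3% at n = 130. That rule does not keep the 6.6% limit: 5 recurrences among 137 give an upper limit of 7.52% and an attained level of 0.105. It cannot support the power claim, and it is a separate inconsistency.

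**Conclusion.** The point holds in a limited form. The 10% allowance covers two causes of loss, while the article's own evidence on one of them is 15%. If about three quarters or more of that 15% is unassessable, technical failure alone takes the study below 137. At a total loss of 15%, the chance of falling short is 93%.

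The stated power is a best case. Expected power at 153 enrolled is about 80% at 10% loss and about 75% at 15% loss. Put the other way, a procedure with a true 2% rate has a chance of about 20% to 25% of not meeting the limit, against the 14% implied by the article. The error is conservative. A reader might infer that it could make an unsafe procedure look safe; it does not, because under the 6.6% limit the cut-off falls with the number assessed.

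These figures assume a true rate of 2%, the 6.6% confidence-limit rule and independent losses. The share of the 15% that would be lost from the primary analysis is unknown, so a shortfall is a clear risk rather than an established outcome.

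**What to change.** In the Sample size section:

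1. Align the drop-out assumption with the 85% figure, or state which part of the 15% is expected to stay assessable and so why 10% is enough.
2. Replace the claim of at least 86% power with the expected power at 153 enrolled: about 80% at 10% loss and about 75% at 15% loss.
3. Give the cut-off that matches the number actually assessed: at most 4 recurrences for n = 137 to 153, and at most 3 for n = 116 to 136.

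This takes a few sentences. The only downside is a less favourable stated power. No extra enrolment, data collection or change to the analysis is needed.

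### The 10% drop-out allowance is not reconciled with the 85% technical feasibility that the protocol reports, so the stated 86% power at 153 enrolled is unsupported

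*Protocol article*

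**What the plan says.** The Sample size section of the protocol article states: "A single sample size of 137 patients will have at least 86% power to detect this non-inferiority limit of 6.6" per cent. The test is specified as "using a one-sided exact test with a significance level of 0.05", and the assumed recurrence rate is 2% over five years. To allow for patients whose primary outcome cannot be assessed, "the sample size will be adjusted to 153 (potential drop-out rate of 10" per cent). The section then names the drop-outs: patients with an indication for additional surgery because of high-risk histology, and patients in whom eFTR is technically impossible.

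The section on statistical methods removes the same two groups from the primary analysis, among them "patients in whom the procedure could not be performed for technical reasons".

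The Background reports that, in the group's earlier multicentre study of scars after R1/Rx resection of T1 CRC, eFTR was "technically feasible in 85% with promising short-term results". The Objectives section sets a feasibility hypothesis of at least 80%.

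**The concern.** One 10% allowance has to absorb two separate sources of loss. For the first of them, technical failure, the protocol's own evidence suggests up to 15%. Nothing in the article explains how technical failure and high-risk histology together would come to 10%.

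The conclusion of this single-arm study turns on one or two events, and the permitted number of events depends on how many patients are evaluable. The planned 137 is the smallest number at which the exact test permits 4 recurrences. A shortfall of a single patient lowers the permitted count to 3. An optimistic allowance therefore alters both the decision threshold and the power.

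**Working it through.** **Inputs.** From Sample size: one-sided exact test, alpha 0.05, limit 6.6%, true rate 2%, 137 evaluable, 10% allowance, 153 enrolled. From Background: 85% technically feasible. From Objectives: at least 80% feasible.

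**Formulas.** For n evaluable patients, the permitted count c is the largest x with P(X ≤ x | n, 0.066) ≤ 0.05. This is equivalent to an exact one-sided 95% upper limit of at most 6.6%. Power is P(X ≤ c | n, 0.02). Enrolment is n/(1 − d), where d is the drop-out proportion.

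**Reproducing the plan.** At n = 137, c = 4, with P(X ≤ 4 | 137, 0.066) = 0.048. The upper limit for 4/137 is 6.56%. Power is 0.859, which rounds to the stated 86%. Enrolment is 137/0.90 = 152.2, rounded up to 153. Both figures reproduce.

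**Putting in the 85%.** 153 × 0.85 = 130.05, so about 130 evaluable, 7 short of 137.
- With 4 events, P(X ≤ 4 | 130, 0.066) = 0.064, above 0.05; the upper limit for 4/130 is 6.90%. Four events are not permitted.
- With 3 events, P(X ≤ 3 | 130, 0.066) = 0.025. So c = 3.
- Power = P(X ≤ 3 | 130, 0.02) = 0.737.

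If each patient is evaluable independently with probability 0.85, the chance that at least 137 of 153 are evaluable is about 7%.

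**How power moves with the evaluable number.**

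| Evaluable n | Permitted count c | Power at 2% |
|---|---|---|
| 116 | 3 | 79.7% |
| 122 | 3 | 77.2% |
| 130 | 3 | 73.7% |
| 136 | 3 | 71.0% |
| 137 | 4 | 85.9% |
| 138 | 4 | 85.6% |
| 153 | 4 | 80.7% |

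Exact power is saw-toothed. Every n from 116 to 136 permits 3 events and gives 71% to 80%. If all 153 were evaluable, c would still be 4 and power 81%. Up to 153 evaluable, about 86% is obtained only at 137 and just above it.

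**Worst-case sensitivity.** At the hypothesised floor of 80%, 153 × 0.80 = 122.4, so about 122 evaluable, with c = 3 and power 77.2%. It exceeds the power at 130 only because of the saw-tooth; the loss of patients is larger.

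**How much of the 15% has to be non-evaluable.** 15% × 2/3 = 10%. If two thirds of the technical failures were procedures that could not be performed, they would use the whole allowance and leave nothing for high-risk histology.

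**The case against.** The strongest reply is that the 85% does not map exactly onto the drop-out definition. The Outcomes section defines feasibility as macroscopically complete en bloc scar excision. The primary analysis drops only procedures that could not be performed and patients needing surgery for high-risk features. A performed but incomplete resection would fail the first definition and could remain evaluable under the second. The Background does not define its 85%, and that study is not available here. This stands: 15% is an upper reading of technical loss, and one cannot say that 153 enrolled is certain to fall short of 137.

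The present study also restricts entry: central pathology review before inclusion, a clearly recognised scar of at most 15 mm, difficult sites excluded, and endoscopists with at least 10 personal procedures. These may lower both kinds of loss. That is plausible, but the article does not offer it as the basis for the 10%.

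Several stronger readings are tempting and not supported:
- A reader might take 80% as the expected feasibility. It is a floor, and a success threshold of at least 80% does not contradict a planning value of 90%.
- A reader might add losses for death or follow-up over five years and arrive at much lower power. The documents give no such rate, so any figure would be an assumption.
- A reader might conclude that 86% is attainable only at 137. This is false beyond the enrolled number: n = 157 permits 5 events with power 90.3%.
- A reader might conclude that a safe procedure must now fail more often. That holds under the stated exact test. The same section also has a rule that declares failure at more than 5 recurrences, which does not match the test: 5/137 has an upper limit of 7.5%. Under that rule at n = 130, power would be about 95% and type I error about 13.5%, so the shortfall would show as type I error. The mismatch is a separate issue.

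**Conclusion.** The point holds as an unsupported planning input. It is not an arithmetic error. The 10% allowance and the reported 85% are not reconciled anywhere in the article, and the stated power depends on that allowance being right.

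If 85% of enrolled patients are evaluable, about 130 are expected, the permitted count is 3, and power at a true 2% is about 74%, roughly 12 percentage points below the stated figure (85.9 − 73.7 = 12.2). This rests on two assumptions: that all of the 15% are lost to the primary analysis, and that no other loss occurs. The first may overstate the loss. The second understates it, because high-risk histology is still to be added. The result also presumes that the stated exact test with the 6.6% limit is the decision rule.

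**What to change.** In the Sample size section:

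1. Reconcile the drop-out allowance with the 85% figure. State what share of those technical failures would be non-evaluable under the primary-analysis definition, and add a separate expected share for high-risk histology. If the authors hold to 10%, give the reason, for example the entry restrictions.
2. State the expected evaluable number and the power that follows from it (about 74% at 130) in place of the claim of at least 86%.
3. State that the permitted count is taken from the exact test at the number actually evaluable (3 for 116 to 136; 4 for 137 to 153), and give the power range that goes with it.
4. Show 80% feasibility (122 evaluable, 77%) only as a worst-case sensitivity figure, and any five-year death or loss rate only as a labelled assumption.

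The cost is a change of wording and a less favourable stated power. No extra enrolment is required. For information, 137 evaluable at 15% loss would correspond to 137/0.85 = 161.2, that is 162 enrolled. The rule of more than 5 recurrences should be settled separately, since it determines whether a shortfall shows as lost power or as type I error.

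### The recurrence count that fails the study is one too high: with 137 evaluable patients, 5 events already push the exact upper limit past 6.6%, but failure is set at more than 5

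*Protocol article*

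**What the plan says.** The Sample size section of the protocol article gives two forms of the safety decision.

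- **Confidence limit.** eFTR is to be qualified as "unsafe if the upper 95% one-sided confidence limit of its related local recurrence rate after five years extends beyond 6.6" percent.
- **Count.** Oncological safety is not established if, over five years, "more than 5 local luminal recurrences are observed -which implies that the upper limit of the confidence interval will exceed the non-inferiority limit".

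The design between them is fully specified. "A single sample size of 137 patients will have at least 86% power to detect this non-inferiority limit of 6.6" percent, "using a one-sided exact test with a significance level of 0.05", "for maximum actually observed local recurrence rates of 2% over five years". For drop-out, "the sample size will be adjusted to 153 (potential drop-out rate of 10" percent). The section on statistical methods for primary and secondary outcomes limits the primary analysis to patients whose primary outcome can be assessed. The planned denominator is therefore 137, not 153.

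**The concern.** The count is offered as the practical equivalent of the confidence-limit criterion. If the two are equivalent, the largest count that does not fail the study must be the largest count whose exact upper limit stays at or below 6.6%. The text puts that count at 5, but the stated sample size, alpha and power put it at 4.

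The decision therefore depends on which sentence is applied if exactly 5 recurrences occur. Five of 137 is 3.6%, a result that could well arise. The discrepancy runs in the permissive direction: a reader who uses the count alone accepts a higher risk of passing a procedure whose true rate sits at the trial's own unsafe limit. If the conflict is settled only after the count is known, either choice will look driven by the data.

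**Working it through.** **Inputs** (all from Sample size): n = 137 evaluable, 153 enrolled; unacceptable rate 6.6%; assumed rate 2%; one-sided exact test, alpha 0.05; stated power 86%; benchmark 1/102 with an upper limit of 4.6%.

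**Formulas.** Let X be the number of recurrences, binomial(n, p).

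- The exact one-sided 95% upper limit for x events is the p that solves P(X ≤ x | n, p) = 0.05, which is the 0.95 quantile of Beta(x + 1, n − x).
- For a rule that passes at c or fewer events, type I error = P(X ≤ c | n, 0.066) and power = P(X ≤ c | n, 0.02).

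**Step 1: reproduce the plan's own figures.**

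- Benchmark 1/102: the exact limit is 4.57%, matching the stated 4.6%. A Wald limit would be 2.59%. The plan's limits are therefore exact ones.
- Largest c at n = 137 with P(X ≤ c | 0.066) ≤ 0.05: c = 4, with type I error 4.81% and power 85.88%. This is the stated 86% after rounding.
- 137 is the smallest n at which 4 events pass: 4/136 gives 6.604%, 4/137 gives 6.557%.
- Drop-out: 137 / 0.90 = 152.2, rounded up to 153.

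Sample size, alpha, power and benchmark all reproduce, and all of them point to a maximum of 4.

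**Step 2: compare the candidate cut-offs at n = 137.**

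| Events | Exact upper limit | P(this many or fewer) at 6.6% | P(this many or fewer) at 2% |
|---|---|---|---|
| 4 | 6.56% | 4.8% | 85.9% |
| 5 | 7.52% | 10.5% | 94.2% |
| 6 | 8.46% | 19.4% | 97.9% |

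The limit is first breached at 5 events, not at 6.

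**Step 3: could a larger denominator rescue the count?** With all 153 evaluable, 5 events give an exact limit of 6.75% and a type I error of 5.7%. Five events pass only from n = 157 (6.58%; at 156 the limit is 6.62%), which is above the planned 153.

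**Step 4: could another interval rescue it?** Limits for 5/137 are Wilson 7.31%, mid-p 7.11%, Jeffreys 7.04% and Wald 6.29%. Only Wald stays below 6.6%, and it contradicts both the stated exact test and the benchmark in Step 1. At n = 153, Wilson (6.56%), mid-p (6.38%) and Jeffreys (6.32%) would admit 5 events, but none of these is the stated exact method.

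**Step 5: smaller denominators.** Minimum evaluable numbers for the exact limit to stay at or below 6.6%:

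| Events allowed | Minimum evaluable |
|---|---|
| 2 | 94 |
| 3 | 116 |
| 4 | 137 |
| 5 | 157 |

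So 4 events are allowed at 137 to 156 evaluable, 3 at 116 to 136, and 2 at 94 to 115.

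**Sensitivity.** At a true rate of 4.5%, with 137 evaluable, the chance of not failing is 26% with a maximum of 4 and 42% with a maximum of 5. The 4.5% is the 4/89 cohort cited in the same section. The protocol notes that histology there was not reassessed before resection and that 3 of the 4 recurrences had high-risk factors on revision. This trial requires central review before inclusion, so the figure shows sensitivity and is not a forecast.

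**The case against.** The strongest reply is that the correct criterion is already written down. The confidence-limit statement comes first, the count follows as its consequence, and at 5 of 137 the first statement already says unsafe. The count sentence is also literally true as an implication, since 6 of 137 has a limit of 8.46%. Both observations stand. They mean the section holds one sound criterion and one that does not match it; they do not remove the mismatch.

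A reader might infer more than the document supports:

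- **That the count is the trial's only decision rule.** It is not, because the confidence-limit criterion stands in the same section.
- **That 5 recurrences would certainly be reported as safe.** The sentence gives a condition for failure and never says that 5 or fewer establishes safety. That is the natural way to use it, but it remains an inference.
- **That 157 evaluable patients are out of reach.** No enrolment cap is stated. The text supports only that 157 is more than the 153 planned.
- **That the Objectives promise proof of a rate below 2%.** The hypothesis of a "low risk of luminal cancer recurrence" under 2% states what is expected. Sample size uses 2% as the assumed rate and tests against 6.6%. Nothing requires the upper limit to fall below 2%, so there is no contradiction.

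The doubling of the error rate is also specific to 137 evaluable patients. At 153 the excess is small, 5.7% against 5%.

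**Conclusion.** The point holds. The count is one event too permissive for the exact test, alpha and power stated beside it, and the two criteria disagree at exactly 5 recurrences. Applied on its own with 137 evaluable, the count carries a type I error of 10.5% instead of 4.8%. Its power at 2% would be 94.2%, not the stated 86%.

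These figures assume that the evaluable patients have complete five-year follow-up and that recurrences are analysed as a simple binomial count, as the exact test implies. The correction is needed even though the sound criterion is present, because the mismatched number is the easiest part of the rule to apply and bears directly on the primary outcome.

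**What to change.** In Sample size, change the count to 'more than 4 (5 or more) local luminal recurrences among 137 evaluable patients'. Add one sentence saying that the decision rests on the exact (Clopper-Pearson) one-sided 95% upper limit at the actual number evaluable, and that this limit governs if it and the count disagree. The protocol could note that the allowed count is 3 at 116 to 136 evaluable and lower below that.

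The cost is a short protocol correction and one fewer tolerated event. The sample size of 137 (153 enrolled), alpha and power do not change. The correction should be made before five-year recurrence counts are known.
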